### Statistical methods

Participant demographics and characteristics are summarized with descriptive statistics. Categorical variables are expressed as median (interquartile range), and continuous variables are expressed as mean (standard deviation). Internal model validation will be performed with 5-fold cross-validation. Cox-regression model was fitted to estimate the hazard rates, hazard ratios (HR) and the 95% CIs. Survival probabilities from any event for the first time since SE will be evaluated using Kaplan–Meier curves. Performance evaluation for the model will include measurements of Accuracy alongside Sensitivity and Specificity, using receiver Operating Characteristic (ROC) analysis with c-statistics, together with calibration plots and risk reclassification. The study will perform comparative assessments between ML models and the QRISK3 calculator to evaluate their incremental predictive value. Statistical analyses will be performed using Stata 18.0 (StataCorp LP, College Station, TX) and the R environment (R 4.5.1, The R Foundation for Statistical Computing, http://www.R-project.org) using R studio (version 2024.12.1). All tests were two-sided and α was set at 0.05, unless specified otherwise.

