### Outcomes

All-cause death, hard endpoints: cardiovascular death, non-fatal myocardial infarction (MI) and composite outcomes will provide with different major cardiovascular events (MACEs), including stroke and unplanned revascularization, and hospital admission with progressive angina (MACE, 3-4-5) across four time periods: 1–3 years, 3–5 years, 5–10 years, and 10–20 years. The outcome data will be derived from NHS -England database with linking patients’ data such as NHS number and DOB and date of SE over 17 years after the indexed SE. (DARS-NIC-662451-S5L8J-v0.16).

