### Sample size calculation

The study aims to include approximately 2300 patients undergoing SE for the assessment of inducible myocardial ischaemia. The sample size was determined based on anticipated event rates, longitudinal outcome modelling requirements, and the complexity of the proposed ML framework.

Previous SE studies and cardiovascular outcome registries suggest that MACE are expected to occur at sufficient frequency within long-term follow-up to support robust prognostic modelling.^12^ The projected cohort size is anticipated to provide an adequate number of outcome events to satisfy event-per-variable requirements for both conventional statistical analyses and ML-based predictive modelling, while reducing the risk of model overfitting. The proposed sample size is also considered sufficient to support internal cross-validation, subgroup analyses, calibration assessment, and the evaluation of multiple supervised ML approaches, including ensemble methods, support vector machines (SVMs), and neural networks. In addition, linkage with longitudinal NHS outcome datasets over extended follow-up periods is expected to strengthen survival modelling and time-to-event prediction analyses.

External validation using independent multicentre SE cohorts is planned to further assess model generalisability and robustness across different clinical settings.

*
Table 1
* shows the characteristics of the patient population.

**Table 1 qyag143-T1:** Population characteristics

Variable	Total	Positive SE	Negative SE	*P*-value
Anthropometric variables				
*N*	2263	371 (16%)	1892 (84%)	—
Age (years)	63 (55–72)	64 (57–72)	63 (54–72)	0.031
Male Sex	1201 (53%)	243 (65%)	958 (51%)	<0.0001
Race				
Caucasian	2048 (91%)	330 (89%)	1718 (91%)	0.42
Asian	152 (7%)	27 (7%)	125 (7%)	0.85
Black	39 (2%)	8 (2%)	31 (2%)	0.71
Other	24 (1%)	6 (2%)	18 (1%)	0.31
Height (cm)	167 (160–175)	168 (160–176)	167 (160–175)	0.285
Weight (kg)	80 (68–95)	82 (70–98)	79 (67–94)	0.009
BMI (kg/m^2^)	28.7 (24.8–33.5)	29.0 (25.1–33.9)	28.6 (24.7–33.4)	0.198
BSA (m^2^)	1.90 (1.75–2.08)	1.93 (1.78–2.11)	1.89 (1.74–2.07)	0.012
Cardiovascular risk factors factors				
Hypertension	1371 (61%)	240 (65%)	1131 (60%)	0.072
Dyslipidaemia	1345 (59%)	238 (64%)	1107 (59%)	0.031
Current Smoker	218 (10%)	44 (12%)	174 (9%)	0.092
Former Smoker	648 (29%)	114 (31%)	534 (28%)	0.285
Diabetes Mellitus	671 (30%)	127 (34%)	544 (29%)	0.036
Obesity (BMI ≥30)	232 (10%)	30 (8%)	202 (11%)	0.142

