### Stage 2: machine learning model development

The cohort is divided into training and validation sets, with 20% of the data held out for internal validation. Supervised machine learning models are developed using demographic characteristics, clinical risk factors, physiological measurements obtained during SE, and imaging-derived variables. The evaluated algorithms include ensemble methods (Random Forest and Gradient Boosting), SVM, and artificial neural networks (ANNs). Hyperparameter optimizations are performed using Bayesian optimization within nested cross-validation. Model selection is based on discrimination, calibration, robustness across validation folds, and clinical interpretability. SHapley Additive exPlanations (SHAP) is subsequently used to quantify feature importance and improve model transparency.

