#### Model development and evaluation

Selected features will then be used for prognostic modelling using approached such as logistic regression, LASSO regression (Least Absolute Shrinkage and Selection Operator), Cox survival model, and Random Forest survival model. Hyperparameters will be optimized using grid search and random search strategies. Model performance will be evaluated using accuracy, sensitivity, specificity, true positive rate, and true negative rate. A five-fold cross-validation strategy will be employed to ensure robustness and reduce sampling bias. In each iteration, models will be trained on four folds and will be evaluated on the remaining fold, with the process repeated until all folds were used for validation.

To minimize overfitting, model development incorporates a held-out validation cohort for internal performance assessment, and final model performance will be further evaluated in geographically distinct external validation cohorts with long-term clinical follow-up (including EVAREST and Stress Echo 2030, where available) to assess generalisability.

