### Stage 3: model evaluation, longitudinal risk prediction using NHS England (aka digital) data

In the final stage, the local Hospital dataset was linked with NHS England longitudinal records, which include confirmed cardiovascular events. The performance of ML score to predict clinical events will be evaluated against base models of QRISK3, and SE ischaemia positivity. The forecasting power of future cardiovascular events over 5-year and 10-year will be assessed.

This longitudinal modelling framework enables dynamic risk prediction and supports early identification of individuals at elevated risk of adverse cardiovascular outcomes. We will be inviting external sites for validation and testing the robustness and scalability of the developed predictive algorithm in all spectra of SE modalities.

Internal validation once completed external validation is performed using independent multicentre cohorts, including EVAREST and Stress Echo 2030 to assess generalisability of the model. Model discrimination will be assessed using the area under the receiver operating characteristic curve (AUC) with 95% confidence intervals (CIs). Calibration will be evaluated using calibration-in-the-large, calibration slope, observed-to-expected event ratios, calibration plots, and the Brier score. Where systematic miscalibration is identified, model recalibration using intercept and slope adjustment will be undertaken prior to assessing clinical utility by. using risk reclassification analyses, including the net reclassification improvement (NRI).

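### For 5- and 10-year MACE and cardiovascular death the plan names no competing-risk estimator and no censoring-adjusted metric, so absolute risk may be misstated, chiefly at 10 years and beyond

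*Protocol article*

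**What the plan says.** The Outcomes section lists "All-cause death, hard endpoints: cardiovascular death, non-fatal myocardial infarction (MI) and composite outcomes will provide with different major cardiovascular events (MACEs", with stroke, unplanned revascularisation and admission for angina as further components, assessed "across four time periods: 1–3 years, 3–5 years, 5–10 years, and 10–20 years". Cardiovascular death is the only death named within MACE, there and in the Abstract; all-cause death is a separate outcome. Linkage is described as running over 17 years after the index test. The article gives no accrual dates, minimum follow-up or data cut-off.

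Stage 2 names the learners: "The evaluated algorithms include ensemble methods (Random Forest and Gradient Boosting), SVM, and artificial neural networks (ANNs". No survival form of these is mentioned. Model development and evaluation adds logistic and LASSO regression, a Cox model and a random survival forest, and states: "Model performance will be evaluated using accuracy, sensitivity, specificity, true positive rate, and true negative rate".

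Stage 3 sets horizons of 5 and 10 years and states: "Model discrimination will be assessed using the area under the receiver operating characteristic curve (AUC) with 95% confidence intervals (CIs". Calibration is by intercept and slope, observed/expected ratios, plots and the Brier score, with recalibration before net reclassification is assessed. Statistical methods adds Cox regression, c-statistics and the Kaplan–Meier sentence: "Survival probabilities from any event for the first time since SE will be evaluated using Kaplan–Meier curves".

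The reclassification section checks absolute-risk categories against observed event rates and ignores changes below a threshold expected to lie between 3 and 5 percentage points. Competing risks, cumulative incidence, censoring, and time-dependent or weighted versions of the metrics are mentioned nowhere.

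**The concern.** Two separate problems arise when the named methods are applied to MACE or cardiovascular death at a fixed horizon.

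First, a patient who dies of a non-cardiovascular cause can no longer have a MACE. Kaplan–Meier, or a risk computed from a single Cox model, treats that death as censoring. It therefore estimates the risk in a population where such deaths do not occur, which is higher than the risk patients actually face. The median age is 63, so such deaths will not be rare over 10 years or more.

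Second, a yes/no classifier, ordinary AUC, the Brier score, sensitivity and specificity all need each patient's status at the horizon. A patient censored earlier has none. If such patients are coded event-free, observed risk is too low; if they are dropped, it is too high.

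The stakes are in the absolute scale. QRISK3, the benchmark, is a 10-year risk. Categories are checked against observed rates, and models are recalibrated to observed risk. If observed risk is wrong, recalibration builds the error into the final model.

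**Working it through.** **The plan's own figures.** The article states no 5- or 10-year risk and no event rate, so there is no figure to reproduce. Every rate and follow-up pattern below is an assumption.

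**1. Kaplan–Meier against cumulative incidence.** Take constant yearly hazards: *m* for MACE (1–3%) and *d* for non-cardiovascular death (0.5–3%).

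- One minus Kaplan–Meier: 1 − exp(−*m·t*).
- Cumulative incidence, which Aalen–Johansen estimates: *m*/(*m*+*d*) × [1 − exp(−(*m*+*d*)·*t*)].

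Example with *m* = *d* = 0.02 and *t* = 10: 1 − exp(−0.2) = 18.1%; 0.5 × [1 − exp(−0.4)] = 16.5%. The gap is 1.6 points.

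| Horizon | 1−KM vs cumulative incidence, *m* = *d* = 2% | Gap over the assumed range (points) | Ratio |
|---|---|---|---|
| 5 years | 9.5% vs 9.1% | 0.1–1.0 | 1.01–1.08 |
| 10 years | 18.1% vs 16.5% | 0.2–3.4 | 1.02–1.16 |
| 17 years | 28.8% vs 24.7% | 0.6–8.0 | 1.04–1.27 |

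At 10 years only the extreme corner (3% and 3%) passes 3 points on average.

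**2. Where the average hides the error.** A simulated cohort had age with mean 63 and SD 12, a MACE hazard of 0.02·exp(0.04(age−63) + 0.6*x* − 0.25) with *x* standard normal, and a non-cardiovascular death hazard of 0.012·exp(0.09(age−63) − 0.5). Non-cardiovascular death by 10 years was 9.5%. Predicted 10-year risk ignoring competing death averaged 17.7% against 16.4% observed (O/E 0.93). At age 75 and over it was 30.5% against 25.2% (O/E 0.83). About 12% of patients had a predicted risk more than 3 points too high.

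**3. Yes/no labels with incomplete follow-up.** Take *m* = 0.02, *d* = 0.01, *h* = *m* + *d* = 0.03, and censoring uniform on (*a*, 17) years. Let *I* be the probability of being censored before the horizon *T* while event-free: *I* = [exp(−*ha*) − exp(−*hT*)]/[*h*(17−*a*)] for *a* < *T*.

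- True risk: (*m*/*h*)·[1 − exp(−*hT*)].
- Censored coded event-free: (*m*/*h*)·[1 − *I* − P(C ≥ *T*)·exp(−*hT*)].
- Censored dropped: the previous figure divided by (1 − *I*).

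For *a* = 1, *T* = 10: *I* = (0.9704 − 0.7408)/0.48 = 0.478 and P(C ≥ 10) = 7/16. True risk is 0.667 × 0.2592 = 17.3%. Coded event-free: 0.667 × (1 − 0.478 − 0.324) = 13.2%. Dropped: 0.1317/0.5216 = 25.2%.

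| Follow-up | 5 years: true / event-free / dropped | 10 years: true / event-free / dropped |
|---|---|---|
| 1–17 years | 9.3 / 8.4 / 10.9% | 17.3 / 13.2 / 25.2% |
| 5–17 years | 9.3 / 9.3 / 9.3% | 17.3 / 15.7 / 23.5% |
| 10–17 years | 9.3 / 9.3 / 9.3% | 17.3 / 17.3 / 17.3% |

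A simulation of two million patients agrees to within 0.1 point (25.3% in place of 25.2%).

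**The case against.** The strongest reply is that the documents do not establish bias, and much of it stands.

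- A reader might infer that the Kaplan–Meier sentence is itself wrong. It concerns survival curves for *any event*, which is undefined. If all-cause death is included, nothing competes and Kaplan–Meier is valid for that composite. In that case, however, no estimator of observed MACE risk is named.
- A reader might infer that follow-up is staggered. Consecutive recruitment makes this likely, but no dates are given, and the 17 years could be read as a minimum. With at least 10 years for everyone, the labelling problem disappears at both horizons.
- A reader might infer that the plan ignores survival methods. It does not: Cox, a random survival forest and c-statistics are named, and these handle right censoring. They do not by themselves give a risk that allows for competing death, and the evaluation step scores them with the same binary measures.
- A reader might infer that the classifiers mishandle competing death. With complete follow-up they do not, because death before MACE is correctly a non-event. Their exposure is to censoring only.
- A reader might infer that models are chosen on accuracy. Stage 2 bases selection on discrimination, calibration, robustness across folds and interpretability. Listing sensitivity and specificity alongside the true positive and true negative rates is harmless repetition.

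It can also be said that weighted metrics are detail for an analysis plan that is not shown. That has force for the implementation. But the article does fix which metrics and which estimator are used, and a later document would have to change those choices rather than fill a gap.

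**Conclusion.** The point holds in a limited form. For MACE and cardiovascular death, the named estimator and metrics allow neither for competing death nor for incomplete follow-up, so absolute risk may be misstated. The documents do not support saying that it will be.

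The competing-death error is small at 5 years (at most about 1 point). At 10 years it is 0.2–3.4 points on average and larger in older patients, and it grows beyond that. The labelling error could be larger at 10 years, about 4 points down or 8 points up in the 1–17-year example, but it depends wholly on follow-up that the article does not describe. The two errors can run in opposite directions, so no single net bias can be stated. Both can reach the 3–5-point scale on which the framework reclassifies patients, which is why the point deserves action before performance results are produced.

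**What to change.** 1. Define *any event* in Statistical methods. Keep Kaplan–Meier only for all-cause death or composites that include it.
2. Estimate observed MACE and cardiovascular-death risk with Aalen–Johansen, taking the deaths outside the endpoint as competing events. Predict cumulative incidence from combined cause-specific models, Fine–Gray or a competing-risk forest. Cox can stay for cause-specific hazard ratios.
3. At 5 and 10 years, use IPCW time-dependent AUC and Brier score, with observed/expected ratios and calibration based on Aalen–Johansen. Use these observed risks for recalibration and for checking the risk categories.
4. State the censoring date and the number of patients with complete follow-up at each horizon. Where follow-up is incomplete, give the Stage 2 classifiers inverse-probability-of-censoring weights or replace them with survival versions.

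The cost is modest extra programming in R, which is already named. No new data are needed beyond date and cause of death, which the cardiovascular-death endpoint already requires.

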### Stage 1: clinical risk modelling and baseline assessment

#### QRISK3 risk estimation

QRISK3 is a validated clinical risk prediction model designed to estimate the 10-year risk of cardiovascular disease (CVD) using demographic and clinical variables.^11^ In this study, QRISK3 is used as a benchmark model against which ML-based approaches are evaluated.

Relevant patient characteristics and CAD risk factors were extracted from the local Hospital dataset and processed using the QRISK3 framework. The resulting risk estimates provide a clinically interpretable baseline for comparison with ML predictions (details of data extraction is provided in the Supplement).

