**Figure 2 qyag143-F2:**
[figure not shown]
FINESSE—machine learning model development workflow.

Baseline risk for each patient will be defined using conventional clinical assessment and QRISK3 derived estimates, as previously described. FINESSE AI will then generate an updated, individualized probability of the outcome of interest at a specified time horizon by integrating echocardiographic parameters, haemodynamic response variables, clinical characteristics, and longitudinal data. The integrated risk estimate will be defined as:

$$R_{F}(i,t)=f(R_{0}(i,t),X_{e}(i),X_{h}(i),X_{c}(i),X_{l}(i))$$

where $R_{0}(i,t)$ represents the baseline risk estimate and the additional inputs correspond to echocardiographic, haemodynamic, clinical, and longitudinal variables, respectively.

To facilitate clinical interpretation, continuous risk estimates will be mapped to predefined categories using a threshold-based classification function. These thresholds will be prespecified and subsequently evaluated against observed event rates within the study cohort to ensure appropriate calibration defined as low risk–intermediate risk–high risk.

Risk reclassification will be defined as a change in category between baseline and FINESSE-derived estimates, expressed as the difference between the categorical assignments derived from $R_{F}(i,\;t)$ and $R_{0}(i,\;t)$. Reclassification will therefore reflect either upward or downward movement across predefined risk strata. To minimize clinically insignificant shifts, reclassification will only be considered when the absolute change in predicted risk exceeds a predefined threshold, anticipated to be in the range of 3–5 percentage points. The predefined 3–5% risk reclassification threshold was selected because it represents the range within which relatively small improvements in estimated cardiovascular risk may influence guideline-directed management decisions, including initiation or intensification of lipid-lowering therapy, additional diagnostic testing, or referral for invasive coronary angiography. Similar thresholds have been adopted in previous cardiovascular risk prediction studies evaluating improvements in discrimination and clinical utility through net reclassification analyses. The threshold was therefore chosen to maximize clinical relevance rather than statistical optimization alone.

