In instances where FINESSE-derived risk estimates are discordant with conventional diagnostic findings, such as a low-risk SE profile in the presence of an elevated predicted risk, cases will be flagged for clinical review rather than automatically reassigned. This approach is intended to preserve alignment with established diagnostic pathways and ensure that model outputs are interpreted within the broader clinical context.

Rather than replacing current clinical assessment, the FINESSE framework is intended to function as a decision-support system embedded within routine SE reporting. Following completion of image interpretation, the algorithm automatically integrates demographic, clinical, laboratory, ECG and echocardiographic parameters to generate an individualized risk estimate. This risk estimate may assist clinicians in identifying patients who would benefit from intensified preventive therapy, further anatomical imaging, closer surveillance, or expedited invasive investigation while preserving final clinical judgement.

The incremental value of the FINESSE AI reclassification framework will be evaluated by comparing baseline and model-derived predictions using discrimination metrics, including the AUC, alongside calibration assessment using calibration plots and Brier scores. In addition, reclassification-specific metrics, including NRI and integrated discrimination improvement, will be used to quantify the extent to which FINESSE AI enhances patient stratification beyond conventional approaches.

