### Expected outcomes

Development of a robust ML-based predictive model for adverse outcomes in SE. Identification of significant predictors, including echocardiographic, clinical, and demographic variables. Demonstration of the incremental value of ML over traditional statistical methods in improving diagnostic accuracy and risk stratification (*Figure 2*). Insight into the feasibility of integrating ML models into clinical workflows to personalize patient care and optimize resource utilization. (*Figure 2*).

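### The named comparators for the ML models lack the ML models' predictors, so the stated comparisons do not by themselves support a claim of ML's incremental value over traditional statistical methods

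*Protocol article*

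**What the plan says.** **The claim.** Expected outcomes in the protocol article lists: "Demonstration of the incremental value of ML over traditional statistical methods in improving diagnostic accuracy and risk stratification". The Key messages and the Introduction likewise promise better diagnosis and prognostication than traditional methods.

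**The comparators.**
- QRISK3 risk estimation (Stage 1): "QRISK3 is used as a benchmark model against which ML-based approaches are evaluated". Baseline performance evaluation uses the QRISK3 results as the yardstick for what ML adds.
- Statistical methods: "The study will perform comparative assessments between ML models and the QRISK3 calculator to evaluate their incremental predictive value".
- Stage 3: "The performance of ML score to predict clinical events will be evaluated against base models of QRISK3, and SE ischaemia positivity".
- FINESSE AI–based risk reclassification framework: "Baseline risk for each patient will be defined using conventional clinical assessment and QRISK3 derived estimates, as previously described". The framework's value is then "evaluated by comparing baseline and model-derived predictions using discrimination metrics, including the AUC", with calibration, NRI and IDI alongside.

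**The ML inputs.** Stage 2: "Supervised machine learning models are developed using demographic characteristics, clinical risk factors, physiological measurements obtained during SE, and imaging-derived variables".

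**The conventional regressions.** Model development and evaluation, within Stage 2, plans prognostic modelling on the selected features with approaches such as "logistic regression, LASSO regression (Least Absolute Shrinkage and Selection Operator), Cox survival model, and Random Forest survival model". It does not say that any of these is the reference for measuring what ML adds.

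**The concern.** A claim that ML improves on traditional statistical methods is a claim about the algorithm. Testing it requires two models that differ in algorithm and agree in everything else: candidate predictors, endpoint, horizon and data used for fitting. The references that the article names differ from the ML models in more than the algorithm. QRISK3 contains no stress echo information and was not developed in this cohort. SE positivity is a single binary finding. The clinical-plus-QRISK3 baseline is by construction one of the inputs to the FINESSE estimate.

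At stake is the attribution of the headline result. If stress echo carries prognostic information beyond QRISK3, almost any sensible model that uses it will outperform QRISK3, an ordinary regression included. Reporting that gain as the value of ML could lead readers to prefer a complex algorithm where a transparent regression would do as well.

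**Working it through.** The article gives no AUC, event rate or expected gain, so there is no figure to reproduce. The check has three parts.

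**1. What each stated comparison can isolate**

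| Section | Reference | What differs from the ML model |
|---|---|---|
| Stage 1; Statistical methods | QRISK3 | predictors, local fitting, algorithm |
| Stage 3 | QRISK3 and SE positivity (separate or joint not stated) | predictors (wall motion scores, stage-wise haemodynamics, other clinical variables), algorithm; local fitting for QRISK3 |
| Reclassification framework | clinical assessment plus QRISK3 (R0) | predictors, local fitting, algorithm |

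The framework's formula shows the mixing directly. R_F is a function of R0 and of echocardiographic, haemodynamic, clinical and longitudinal inputs. Comparing R_F with R0 measures all the added data and the fitting together. No row isolates the algorithm.

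**2. How large a gain could arise with no ML contribution**

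All inputs here are assumptions. Take two normally distributed scores that are independent given outcome, with equal variances in patients with and without events. Then d = √2 × z(AUC), the best combination has d = √(d1² + d2²), and AUC = Φ(d/√2). In this model a plain logistic regression is the optimal combination, so no algorithm can add anything.

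- QRISK3 at AUC 0.68: d1 = 0.661.
- SE information at AUC 0.60: d2 = 0.358. Combined d = √(0.661² + 0.358²) = 0.752, AUC 0.703, gain 0.703 − 0.68 = 0.023.
- SE information at AUC 0.70: d2 = 0.742. Combined d = √(0.661² + 0.742²) = 0.994, AUC 0.759, gain 0.759 − 0.68 = 0.079.

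Varying both inputs over 0.60 to 0.70 gives combined AUCs of 0.64 to 0.77, a gain of 0.02 to 0.12 over either input alone.

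A simulation used the Table 1 size of 2263, an 80/20 split, both inputs at an assumed AUC of 0.65, assumed event rates of 10%, 20% and 30%, and 300 runs per rate. Mean held-out AUC was about 0.65 for QRISK3 alone and 0.704 to 0.707 for plain logistic regression on both inputs. The regression beat QRISK3 alone in 97% to 99% of runs.

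**3. Whether the diagnostic part of the claim has an endpoint**

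Every item under Outcomes is a later event: death, MI, stroke, unplanned revascularization, or admission with progressive angina. Data collection lists no coronary reference standard. The stated endpoints can therefore support statements about prognosis and risk stratification. Nothing listed allows diagnostic accuracy to be measured.

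**The case against.** The strongest reply is that the main question is a different one. The article's aims centre on what the whole package of multimodal data and model adds to current assessment, and QRISK3 and SE positivity are reasonable references for that. The sentence in Statistical methods is not wrong in itself, since it promises value relative to QRISK3. The wording about traditional statistical methods as the thing to be beaten stands in the Expected outcomes list. The details of benchmarking can be left to an analysis plan. All of this is fair, and the package comparison should stay. But the article fixes both the claim and the comparators, and they do not match, so this is more than a detail deferred.

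A reader might infer that the study cannot show an ML gain at all, or that QRISK3 alone and SE positivity alone are the only references. The document does not support that. Logistic, LASSO and Cox models on the selected features are planned next to Random Forest survival, with the same metrics and five-fold cross-validation, so a like-for-like comparison is feasible. Stage 3 leaves open whether its base models are separate or joint, and the framework's baseline adds conventional clinical assessment. Even a joint QRISK3 and SE-positivity model would still lack most of the ML predictors.

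A reader might also infer that an ML benefit is almost certain to be reported. That depends on the assumed AUCs and on independence. Table 1 shows higher QRISK3 in SE-positive patients (median 9.6 against 8.1), and such dependence would generally reduce the gain. The simulation did not examine an overfitted ML model with many predictors. Nor does the document say that medication is an ML predictor: medication records are extracted, but the Stage 2 predictor list does not name them.

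**Conclusion.** The point holds as a mismatch between a stated claim and the stated comparisons. None of the named references is a conventional regression on the ML models' predictors, so a gain over them would combine added predictors, local fitting and algorithm. It would not by itself demonstrate incremental value of ML over traditional statistical methods.

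The possible misattribution is illustrated at 0.02 to 0.08 in AUC for QRISK3 at 0.68 and SE information at 0.60 to 0.70. These are assumed values under independence, not estimates for this cohort. The structural conclusion does not depend on them. The diagnostic-accuracy wording is a related but separate fault of the same sentence: no listed outcome or data item can test it.

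**What to change.** 1. Name one of the regressions already planned (Cox, or penalised Cox or logistic) as the reference for the ML comparison. Give it the same candidate predictors, endpoint, horizon and resampling as the ML models, and compare AUC, calibration and NRI. Attribute to ML only the gain over that model.
2. Keep the comparisons with QRISK3, SE positivity and the clinical baseline, and describe them as evidence on the value of the whole package.
3. If no same-predictor reference is adopted, reword Expected outcomes to incremental value over QRISK3 and SE positivity.
4. In either case, limit the diagnostic-accuracy claim, in Expected outcomes and where it recurs in the Key messages and Introduction, to prognosis and risk stratification.

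The cost is wording and one designated contrast, since the regressions are already planned and no new data are needed. The downside for the sponsor is that the apparent gain for ML may be smaller.
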